## Abstract

**Background:**

Colorectal cancer (CRC) is the second most prevalent type of cancer in Europe. A single flexible sigmoidoscopy (FS) screening at around the age of 60 years prevents about one-third of CRC cases. However, FS screens only the distal colon, and thus mortality from proximal CRC is unaffected. Computed tomography colonography (CTC) is a highly accurate examination that allows assessment of the entire colon. However, the benefit of CTC testing as a CRC screening test is uncertain. We designed a randomized trial to compare participation rate, detection rates, and costs between CTC (with computer-aided detection) and FS as primary tests for population-based screening.

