FS is an endoscopic procedure, in which the distal 40 to 60 cm of the colon is inspected. Total colonoscopy is advised in cases of positive findings. FS is less invasive than colonoscopy, and requires only a simple bowel preparation of a single enema within 2 hours prior to the procedure. Three European randomized control trials (RCTs) on FS have been performed [9,13,14]. In the UK, one-time screening with FS significantly reduced the incidence of CRC (by 26%) and associated mortality (by 36%) [13]. In Italy, an 18% reduction in incidence and a non-significant 22% reduction in mortality were reported [9], whereas in Norway, no benefit was observed after 7 years of follow-up [15]. A disadvantage of FS is that it does not examine the proximal colon, but distal findings are used to select a higher-risk group for colonoscopy. Another consideration is that its sensitivity depends on the varied experience of the examiners, that has a major impact on the adequacy of mucosal inspection.

Colonoscopy and CTC are structural examinations allowing inspection of the complete colon, and enabling early detection of advanced adenomas (that is,, adenomas ≥10 mm or with unfavorable histological features) and CRC [16]. Although colonoscopy is the most complete endoscopic procedure available for CRC screening [17,18], direct evidence about its effectiveness, complications, and acceptability among individuals at average risk of CRC is still not adequate to justify its use for population screening [19]. Observational evidence suggests that colonoscopy might not be as effective in the proximal colon as in the other segments of the colon and rectum [20,21]. Furthermore, colonoscopy capacity is a limiting factor for its widespread use as a primary screening test.

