### Data analyses

The primary endpoint of the study 1, the detection rate of the screening test, is defined as the proportion of screened subjects with advanced neoplasia divided by the total number of screened subjects. Advanced neoplasia comprises all cancers and advanced adenomas together. The most advanced detected lesion per screened subject will be used to calculate the detection rate. The overall prevalence of polyps of any histology will also be calculated. Detection rates and detection rate differences will be calculated, and all proportions will be reported with 95% confidence interval (CI). Differences in proportions between screening strategies will be calculated using the χ^2^ test. Multivariate logistic regression models with advanced neoplasia as a function of sex, center, and screening test will be used to analyze the differences in detection rate between screening tests. Odds ratio (OR) and its 95% CI will be used as a measure of the association between detection and the variables under evaluation. As a secondary analysis, we will calculate referral rate for each screening test, defined as the proportion of screening tests referred for colonoscopy because of an abnormal result. For the comparison topic, we will use the number of diagnostic colonoscopies induced by each screening test as a proxy for resource utilization and costs.

The primary endpoint of study 2, the participation rate for the screening test, is defined as the number of participants undergoing the screening test relative to the total number of invitees. The χ^2^ test will be used to test if the CTC group achieves a statistically significant difference in participation compared with the FS group. Multivariate models will be fitted to the data, with participation as a function of sex, screening test, and sociodemographic characteristics. All statistical tests will be two-sided and considered statistically significant at *P* < 0.05.

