When comparing FS and CTC as CRC screening strategies, an important issue needs to be considered. FS-detected polyps 6 mm or smaller can be removed immediately, whereas such lesions are usually ignored during CTC screening. Because the long-term implications of removing diminutive polyps are unknown, long-term follow-up of very large samples would be required to estimate the protection of CTC screening against death. To our knowledge, no such trials are planned or ongoing. However, our study will provide indirect evidence of the long-term benefit from CTC screening by comparing the detection rates for CTC versus FS and assuming long-term efficacy of FS screening consistent with the results from the SCORE trial [9]. Of note, the SCORE trial evaluated the protection for FS screening over time in the same screening setting.

One more issue we kept in mind while planning the trial is that overall costs of CTC screening could be affected by uncritical reporting of extracolonic findings [37]. Whether the visualization of extracolonic structures and potential pathology is a real benefit or a disadvantage is still under debate. On the one hand, CTC may incidentally identify asymptomatic malignant diseases or other clinically important conditions, thus possibly reducing mortality. On the other hand, CTC may reveal numerous findings of no clinical relevance, which could result in costly additional diagnostic examinations with an overall negative impact on cost-effectiveness [39]. However, in some cases, detection of relevant extracolonic findings such as abdominal aortic aneurysms (AAA) and extracolonic masses at an early stage may be beneficial. According to one study, the net effect from detection of both AAAs and extracolonic cancers appears to be positive in term of life-years gained and overall cost-effectiveness [38]. Furthermore, cost-effectiveness analyses have also shown that screening for AAA provides high clinical efficacy at a relatively low cost [60]. Based on these considerations, we decide to report and follow only potentially important extracolonic findings such as abdominal and pelvic masses, and AAA larger than 4 cm, which represent only a minority of all extracolonic findings. This study will provide new knowledge on this topic through a separate analysis of the additional costs created by referring patients wtih important extracolonic findings for second-level tests.

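### The Discussion draws long-term CTC benefit from a site-pooled detection comparison and an FS trial's efficacy, which gives no direct support for benefit from extra proximal yield

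*Protocol article*

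**What the plan says.** The inference is in the Discussion, in the paragraph on diminutive polyps. It says that "our study will provide indirect evidence of the long-term benefit from CTC screening by comparing the detection rates for CTC versus FS", while "assuming long-term efficacy of FS screening consistent with the results from the SCORE trial". The Background gives that trial's results: "an 18% reduction in incidence and a non-significant 22% reduction in mortality were reported". It gives no breakdown by site.

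The detection rate is defined under Data analyses. It "is defined as the proportion of screened subjects with advanced neoplasia divided by the total number of screened subjects". The same section adds that "Advanced neoplasia comprises all cancers and advanced adenomas together" and that "The most advanced detected lesion per screened subject will be used to calculate the detection rate". The article names no detection rate by site.

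Two statements elsewhere bear on site. The abstract says that "FS screens only the distal colon, and thus mortality from proximal CRC is unaffected". The Background says that "Observational evidence suggests that colonoscopy might not be as effective in the proximal colon" as in the rest of the large bowel.

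Lesion location is collected in six segments, both at CTC (section CTC lesions) and at colonoscopy (section Second-level colonoscopy).

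**The concern.** The inference has two parts: a comparison of yield, and an efficacy borrowed from FS. Joining them assumes that what CTC detects carries a benefit comparable to what FS detects. By the article's own account, FS does not change proximal mortality. The abstract's reason for looking at CTC is that it shows the whole colon, so additional proximal yield is one expected source of any CTC advantage. It is also the part for which the FS trial offers no direct evidence.

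The Discussion paragraph raises one comparability problem, the small polyps that FS removes and CTC ignores, and does not mention site. If the inference is carried out as written, CTC could be credited with long-term protection that the FS evidence does not support, and a reader of the pooled rates could not tell how much of the advantage is of that kind.

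**Working it through.** **Inputs**
- Detection rates: 5% for FS and 7% for CTC; 2,500 per arm, two-sided 5%, power 80% (Sample size, study 1).
- Efficacy of the earlier Italian FS trial: incidence reduced by 18%, mortality by 22%, the latter not significant (Background).
- Distal/proximal split of either rate: not given.
- Formula linking detection to long-term benefit: not given.

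**The plan's own figure.** The article states no figure for the extrapolation. The only calculation that uses these rates is the study 1 power. With mean rate 0.06:

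- n per arm = [1.96·√(2·0.06·0.94) + 0.8416·√(0.05·0.95 + 0.07·0.93)]² / 0.02² = 2,213 for 80% power (2,312 with continuity correction).
- With 2,500 per arm, power is 84.6% (83.1% with continuity correction).

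The stated 80% is therefore conservative. It does not bear on this point.

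**The statements side by side**
1. Long-term CTC benefit is to be read from the CTC and FS detection rates plus FS efficacy (Discussion).
2. The detection rate counts a person once, by the most advanced lesion, wherever it lies (Data analyses).
3. FS efficacy does not extend to proximal mortality, for reasons of reach (abstract).
4. Hence a CTC excess made up of proximal lesions enters step 1 through step 2, but has no FS efficacy behind it by step 3.

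**Illustration of scale, under an assumed rule.** Suppose benefit is proportional to detection. Let R be the FS reduction and f the share of the 2-point excess that is proximal.

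- Pooled: R × 7/5 = 1.4R.
- Supported by FS evidence: R × [5 + 2(1 − f)]/5.
- Difference: R × 0.4 × f.

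| f | Supported rate (%) | Ratio | Incidence reduction supported (%) | Unsupported (points) | Mortality reduction supported (%) | Unsupported (points) |
|---|---|---|---|---|---|---|
| 0 | 7.0 | 1.40 | 25.2 | 0 | 30.8 | 0 |
| 0.25 | 6.5 | 1.30 | 23.4 | 1.8 | 28.6 | 2.2 |
| 0.50 | 6.0 | 1.20 | 21.6 | 3.6 | 26.4 | 4.4 |
| 0.75 | 5.5 | 1.10 | 19.8 | 5.4 | 24.2 | 6.6 |
| 1 | 5.0 | 1.00 | 18.0 | 7.2 | 22.0 | 8.8 |

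The table lets the whole 5% in the FS arm carry the FS effect, although some of it may be proximal lesions found at follow-up colonoscopy. It also keeps f between 0 and 1, so CTC is taken to find at least as much distally as FS.

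**The case against.** The strongest objection is that this is one cautious sentence in a Discussion. Long-term benefit is not among the listed objectives or the planned analyses, and the text promises only indirect evidence. That stands, and it limits the weight of the point: no primary or secondary analysis is shown to be wrong.

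A second objection is that detection by site is routine and may be in an analysis plan that is not shown, and that the validated model used for cost-effectiveness may already treat site separately. That is possible, and a missing table would not be a finding. The point is that the published inference joins a site-pooled rate to an efficacy that the same article limits by site, without saying so.

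Three stronger readings are tempting, and the article does not support them:

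- **That FS efficacy will be multiplied by the detection ratio.** No formula or multiplier appears. The ratio of 1.4 as a benefit ratio is an illustration only.
- **That proximal detection brings no benefit.** The abstract ties the lack of proximal effect to the reach of FS. The Background says only that observational evidence suggests colonoscopy may work less well there. Both leave proximal benefit open, and possibly smaller.
- **That the FS arm is purely distal, or that most of the CTC excess is proximal.** Distal findings at FS lead to total colonoscopy, so the FS pathway reaches some proximal lesions. The article does not say how any excess divides by site.

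**Conclusion.** The point holds in limited form. The Discussion carries FS efficacy over to CTC through a detection rate that does not distinguish site, although the article itself says that FS leaves proximal mortality unaffected. Benefit from extra proximal yield is thus unproven by this route.

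How much this matters cannot be established from the article. The range of 0 to 7.2 points of incidence reduction (18% rising to 25.2%) and 0 to 8.8 points of mortality reduction (22% rising to 30.8%) rests on assumed proportionality, on the design rates being observed, and on an unknown proximal share of the excess. The mortality figure also starts from a reduction that was not statistically significant. The lower end is zero, so the illustration shows what could be at stake and not that an overstatement will occur.

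The comparison of detection rates as the primary result of study 1 is unaffected. The change is worth making because it is cheap and the inference would otherwise claim more than its source supports.

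**What to change.** 1. Pre-specify advanced-neoplasia detection separately for the distal colon (rectum to descending colon) and the proximal colon, in both arms.
2. Count each site on its own, so that a person with advanced lesions at both sites contributes to both rates. The most-advanced-lesion rule would otherwise hide the second site.
3. In the FS arm, include proximal lesions found at colonoscopy after a positive FS.
4. In the Discussion's inference, rest the FS trial's efficacy on the distal comparison. State proximal benefit as a separate assumption, with a sensitivity range running from none to the full distal effect.
5. Add a sentence to that paragraph naming site as a second comparability problem beside diminutive polyps.

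The cost is a little more analysis and a benefit statement that may be wider or less favourable to CTC. Segment is already recorded at CTC and at colonoscopy, so no new data, visits or participants are needed. The primary endpoint, test and sample size stay as they are. Trial status reports 2,000 enrolled at the time of writing, against 5,000 planned for study 1, so recruitment was still under way when the article was written.

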## Trial status

The trial started recruitment in December 2010. At the time of writing, 2,000 participants had been enrolled in the study overall.

## Abbreviations

AAA: Abdominal aortic aneurysms; CAD: Computer-aided detection; DR FR-CAD: Double-reading first-reader computer-aided detection; C-RADS: CT Colonography Reporting and Data System; CRC: Colorectal cancer; DICOM: Digital Imaging and Communications in Medicine; FOBT: Fecal occult blood test; iFOBT: Fecal immunochemical test; gFOBT: Guaiac fecal occult blood test; FS: Flexible sigmoidoscopy; CT: Colonography; CTC: RCTRandomized clinical trial; IT: Information technology; ICT: Information communications technology; QOL: Quality of life.
